#### **c. Sample size calculations**

These precision and power estimates are based on a final post-intervention sample size of 300 study participants, 100 in each of the three intervention groups. To achieve this post-intervention sample size, we will oversample by 31% (i.e., 435 participants) to account for attrition. That is, we will allow for up to a 31% drop- out rate.

Our primary analysis is a mixed model regression analysis with repeated measures to evaluate the between group differences across the post-intervention time points with adjustment for covariates. Assuming a two- sided significance level of 0.05, we will have at least 80% power to detect differences between any pair of group means of 0.4 standard deviation units (SD – Effect Size Index) across the three post-intervention time points. In addition, the detectable mean difference between groups is 0.49 SD units with a two-sided significance level of 0.01. In our previous study, we found differences on post-intervention XQ means ranging from 0.80 SDs at the end of radiotherapy to 0.68 SDs at 1 month when comparing the acupuncture group with the standard care group. The associated XQ average values for the two groups at 1 month post radiotherapy were: 32.2 (SD=10.6) for acupuncture group and 41.5 (SD=9.6) for control group. As we do not know the exact differences that will occur between the sham acupuncture group and the other two groups, and given the definition of clinically significant effects (i.e., effect sizes of approximately 0.5 SDs being argued to be clinically meaningful) (25, 86, 87) the current study is still well-positioned to detect clinically significant effects between groups that may be present. We prefer to justify sample size using a paired t-test for simplicity and because it is conservative approach, although the later analyses using repeated measures will have greater power to detect differences between groups.

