### **a. Data analysis**

Our primary objective is to determine if true acupuncture is more effective than sham acupuncture or standard care for preventing radiation-induced xerostomia among cancer patients at M. D. Anderson and Fudan Cancer Hospital. The primary outcome will be self-reported xerostomia symptoms using the Xerostomia Questionnaire (XQ). We will have information available at baseline and at 5 additional points in time (middle of radiotherapy, end of radiotherapy, and 2-4, 5-9, and 10-15 months after the end of radiotherapy).

Our initial analysis will be a repeated-measures analysis of XQ scores over time by acupuncture group, testing for group effects, time effects, and group by time interaction. This will be done using generalized linear mixed model regression (GLMM) (see below for further details). The primary significance level which will be used is

0.05. For sample size justifications, our primary time endpoint is the end of radiotherapy, or 7 weeks. All three arms will be compared at this time point using an analysis of variance, and if the test is significant ( $p < 0.05$ ), we will use a Duncan's Multiple Range Test which controls the type I comparison-wise error rate to determine which groups are different from each other.

At each point in time, we will also be able to determine if xerostomia has occurred (grade 1 or higher on the v3.0 CTCAE) and will classify each patient as either experiencing xerostomia (one or more episodes of xerostomia) or not. A secondary goal is to determine if the proportion of persons who experience xerostomia in the true acupuncture group is less than that in the sham acupuncture group or the standard care group. We will use the

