points. Post-intervention follow-up criterion measures will be regressed onto study intervention condition, time of assessment, a polynomial function of time (for example, quadratic) if appropriate, and the measure of the criterion at baseline. In addition, we will add important covariates, including adaptive randomization variables and selected demographic variables, such as ethnicity and education, as well as suitable baseline health-related variables and medical characteristics. Tests of the interaction of intervention condition with time of measurement will be evaluated to determine whether the effect of intervention condition varied as a function of time. In the case of statistically significant interactions of intervention condition with time, tests of the effect of intervention condition will be conducted at each individual time point. We will use Bonferroni corrections for each set of multiple comparisons where appropriate. Standard methods of model diagnostics will be used to identify influential observations and to determine suitable transformations where necessary.

We will compare compliance with acupuncture between patients randomized to the acupuncture and sham acupuncture groups. Compliance will be measured as the number of times the participants received their scheduled intervention per week. At each assessment after the end of radiotherapy, we will determine if patients in the two groups differ in the number of times they received their scheduled intervention (since the last analysis) using a Wilcoxon rank-sum test. We expect that these frequencies will not be normally distributed so we plan to use a nonparametric test. If there is a statistically significant difference or trend for significance in compliance between any two groups ( $p < 0.10$ ), we will also determine if there is a difference between other outcomes. We will use either t-tests or nonparametric tests such as the Wilcoxon rank-sum test to determine the significance of these differences.

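### The 80% power quoted for 0.4 SD is that of one unadjusted two-sample t-test (not a paired one); the ANOVA-then-Duncan rule at the end of radiotherapy gives about 70–76%

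*Supplement*

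**What the plan says.** All references are to the Final Protocol, section C.6.

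- **c. Sample size calculations.** The sizing rests on a "final post-intervention sample size of 300 study participants, 100 in each of the three intervention groups", and "we will oversample by 31% (i.e., 435 participants) to account for attrition". At a two-sided level of 0.05, the claim is this: "we will have at least 80% power to detect differences between any pair of group means of 0.4 standard deviation units". It is made across three post-intervention time points and follows a sentence naming a covariate-adjusted repeated-measures mixed model as the primary analysis. A companion figure gives 0.49 SD as detectable at two-sided 0.01. The section closes: "We prefer to justify sample size using a paired t-test for simplicity and because it is conservative approach", and adds that the repeated-measures analyses will be more powerful.
- **a. Data analysis.** For sample-size purposes the primary time point is the end of radiotherapy. "All three arms will be compared at this time point using an analysis of variance, and if the test is significant" at 0.05, Duncan's multiple range test then decides which groups differ.
- **a. Data analysis, mixed-model text.** "We will use Bonferroni corrections for each set of multiple comparisons where appropriate". The number of comparisons is not given.
- **Pilot effects (c).** Differences are described as "ranging from 0.80 SDs at the end of radiotherapy to 0.68 SDs at 1 month". The 1-month XQ figures printed beside them are 32.2 (SD 10.6) and 41.5 (SD 9.6).

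**The concern.** The sample-size section makes no allowance for the F test that must be passed first, for Duncan's wider critical range, or for Bonferroni. Each of these makes it harder to declare a given pair different than a lone t-test at 0.05 does. The claim covers any pair of arms, and the section itself says that the position of the sham arm is unknown.

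The test named as the basis does not fit the design either. C.1 describes three parallel randomized groups with no matching between arms.

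The quoted power is what readers will use to interpret a non-significant pair, above all true versus sham acupuncture. If the figure belongs to a more lenient test than the one that will be run, it overstates what such a result says about differences near 0.4 SD.

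**Working it through.** **Inputs.** From C.6 c: 100 per arm, two-sided 0.05, difference 0.4 SD, 31% drop-out. From C.6 a: F test at 0.05, then Duncan. SD is set to 1.

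**1. Sample size.** 435 × 0.69 = 300.15, so 100 per arm is consistent.

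**2. Reproducing the plan's figures.** Two-sample t-test, noncentrality d√(n/2), 198 df.
- d = 0.40: 0.40 × √50 = 2.83, power at 0.05 = 80.4%; the difference detectable with 80% power is 0.398 SD.
- d = 0.49: 0.49 × √50 = 3.46, power at 0.01 = 80.5%; detectable 0.487 SD.

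Both printed figures are recovered with no gate, no multiplicity adjustment and no repeated-measures term.

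**3. Could it be a paired test?** With 100 pairs the noncentrality is 0.40 × √100 = 4.0 (0.4 now in SDs of the difference). Power is 97.7% and the detectable difference 0.28 SD. A paired test cannot be the source of 80% at 0.4.

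**4. The F gate.** Noncentrality λ = 100 × Σ(μᵢ − μ̄)², 2 and 297 df.
- Third arm midway (0, 0.2, 0.4): λ = 100 × (0.04 + 0 + 0.04) = 8.0, power 71.3%.
- Third arm equal to one of the pair (0, 0, 0.4): λ = 100 × (0.0178 + 0.0178 + 0.0711) = 10.67, power 83.7%.

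In the midway case the gate alone caps power for the pair at 71.3%.

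**5. Gate plus Duncan.** Simulation with at least 1 million trials per case. Duncan's critical values are 2.783 (two means) and 2.930 (three means), multiplied by s/√100.

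| Third arm | Power at 0.4 SD | Duncan without the gate | Detectable with 80% power |
|---|---|---|---|
| equals one of the pair | 76% | 79% | 0.42 SD |
| a quarter of the way | 72% | 79% | 0.44 SD |
| midway | 70% | 78% | 0.45 SD |

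Duncan alone costs 1 to 2 percentage points; the gate accounts for most of the loss.

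**6. Bonferroni at one time point.** The number of comparisons is my assumption; this is an alternative to step 5, not an addition to it.
- Two pairs (0.025): 72%; detectable 0.44 SD.
- Three pairs (0.0167): 66%; detectable 0.46 SD.

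**7. Repeated measures.** The plan gives no within-patient correlation ρ, so it is assumed. The mean of three equally correlated measurements has variance (1 + 2ρ)/3, before baseline adjustment. For ρ = 0.7 this is 0.80, SD 0.894, and 0.4/0.894 = 0.447.

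| ρ | Three-pair Bonferroni | Two-pair Bonferroni |
|---|---|---|
| 0.5 | 85% | 89% |
| 0.7 | 77% | 82% |
| 0.9 | 70% | 75% |

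Baseline adjustment adds to these. With ρ = 0.7 and an assumed baseline correlation of 0.3, the variance is 0.80 − 0.09 = 0.71, the effect 0.4/0.843 = 0.475, and three-pair power 83%.

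**8. At 0.5 SD, one time point.** Three-pair Bonferroni 87%; gate plus Duncan 89% (midway) to 93% (third arm equal to one of the pair).

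**9. Pilot effect.** Pooled SD = √((10.6² + 9.6²)/2) = 10.1 with equal weights; (41.5 − 32.2)/10.1 = 0.92. Any weighting keeps the SD between 9.6 and 10.6, so the effect lies between 9.3/10.6 = 0.88 and 9.3/9.6 = 0.97. An effect of 0.68 would need an SD of 9.3/0.68 = 13.7.

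**The case against.** The best defence is that the 80% is claimed for the mixed model across three time points, with the t-test offered only as a simple, cautious stand-in. A reader might infer from step 5 or 6 that the trial's primary analysis has only 66–76% power. The documents do not support that. Those figures are for one unadjusted time point, and step 7 shows that the model can exceed or miss 80% depending on a correlation that the plan does not state. What survives is that the printed numbers come from the t-test, and that C.6 a ties the sizing to the end of radiotherapy, where the gated rule applies.

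It is also fair to say that Bonferroni is left to judgement, sits in the mixed-model text, and is not tied to three arm pairs; the primary aim names two contrasts. The 66% therefore rests on an assumption. The ANOVA-Duncan shortfall does not depend on it.

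A reader might further ask for power to beat both comparators. The plan sets no such joint requirement.

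Paired may be a slip for pairwise. The label is still wrong as printed.

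Finally, the plan concludes only that effects of about 0.5 SD are detectable, and step 8 bears that out.

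**Conclusion.** The point holds as a misdescribed basis. The 80% at 0.40 SD and the 0.49 SD at 0.01 are correct for one unadjusted independent two-sample comparison with 100 per arm, and for nothing else that the section shows. Under ANOVA then Duncan at the end of radiotherapy, a 0.4 SD pair has about 70–76% power and the detectable difference is about 0.42–0.45 SD, the upper end being the case with the third arm midway. These results assume normal data, a common SD and 100 evaluable patients in each arm.

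Whether the mixed model reaches 80% at 0.4 SD is unknown, not refuted. Nor do the documents claim that a null true-versus-sham result would exclude 0.4 SD; that is an inference a reader could draw from the power statement. The shortfall is confined to differences near 0.4 SD and does not show that the trial is too small for its own 0.5 SD benchmark.

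The 0.68 in the pilot text conflicts with the means and SDs beside it, but plays no part in the calculation. C.9 reports that pilot comparison from a mixed model and does not say how the effect was standardized, so the mismatch can be flagged for reconciliation but not resolved in favour of 0.92.

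**What to change.** In C.6 c:

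1. Replace paired by two-sample.
2. Restrict the 80% at 0.40 SD to a single unadjusted pairwise comparison at one time point.
3. Add that under the ANOVA-Duncan rule the difference detectable with 80% power is about 0.42–0.45 SD, depending on the third arm.
4. State which comparisons Bonferroni covers. If it is three arm pairs at one time point, give 0.46 SD.
5. If 80% at 0.4 SD is to be claimed for the mixed model, state the assumed within-patient correlation and any baseline correlation, and show the calculation.
6. Reconcile the pilot 0.68 with the printed means and SDs, which give 0.92, or say how it was standardized.

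The cost is wording and a slightly less favourable figure. Sample size and conduct do not change.

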#### **C.7 Limitations**

There are several challenges with the current study that should be noted. There is the possibility of loss to follow-up to a greater degree than in our pilot studies due to following patients out to 1 year post radiotherapy. Several strategies will be used to decrease the chance of missing data and non-compliance. Forms will be reviewed upon receipt to ensure all items are completed, and if incomplete, participants will be contacted to determine if the question was deliberately skipped and, if not, to get a response. Scheduling of follow-up visits will also coincide with visits to the radiation oncologist, and as such, missing data will be kept at a minimum. Nevertheless, some individuals may fail to complete all questionnaires and

statistical procedures noted above will be implemented. Also, although we will make every effort to recruit minority and underserved participants, as all patients will be recruited from either M. D. Anderson or Fudan Cancer Hospital, the study population will be somewhat select. Nevertheless, the sample will be representative of patients seen at the two hospitals.

### **C.8 Adverse Events**

Acupuncture is a safe technique with few complications. The majority of reported adverse effects are best attributed to insufficient basic medical knowledge, inadequate acupuncture education, or lack of compliance with standardized practice of clean needle technique (104). Several studies by different investigators have shown that most serious adverse events are due to a lack of education or negligence on the part of the practitioner and are not due to the treatment itself (105-109). The side effects most commonly reported when acupuncture is performed correctly by properly trained personnel are relatively minor and include fainting, nausea, vomiting, bruising, and mild discomfort (105-109). In the past, patients occasionally developed contact dermatitis to components in the needles (110, 111), but this currently is rare with improved manufacturing techniques for the stainless steel needles.

For higher risk patients (i.e., those with heart disease or neutropenia), special precautions may be necessary such as avoiding the use of electrostimulation in patients with pacemakers or taking additional measures to prevent infection in patients with compromised immunity (112). Electrical stimulation will not be used in this study, and patients with evidence of infection or compromised immunity will not be included. Although the likelihood of acupuncture-induced infection in this study is low, procedures will be treated as invasive medical procedures and performed using aseptic techniques. The acupuncture needles used will be sterile and individually packaged. Reportable adverse events will include:

- a. syncope
- b. infection at the acupuncture site
- c. allergic contact dermatitis at the acupuncture site
- d. excess bleeding at the acupuncture site

### **C.9 Xerostomia acupuncture research at M. D. Anderson and Fudan Cancer Hospital**

A single-arm pilot study completed at M. D. Anderson assessed whether radiation-induced xerostomia could be reversed using acupuncture (25). A total of 19 patients received 8 treatments over 4 weeks, with weekly assessments during treatment and then at week 5 and week 8 (1 month after treatment). Fifteen patients received IMRT, and subset analysis did not reveal any significant relationship between the amount of radiation received and response to acupuncture. The median interval from completion of radiation therapy to start of acupuncture was 21.5 months. Xerostomia scores, as assessed by the Xerostomia Inventory and the Patient Benefit Questionnaire were significantly better after acupuncture, beginning at week 2 and continuing through week 8. QOL assessed using the FACT-H&N indicated a significant difference in scores for questions related to head/neck cancer at weeks 4 and 8 ( $p=0.04$  and  $p=0.006$ , respectively). At week 8, there was also a significant difference in the physical well-being subscale ( $p=0.04$ ) as well as in the total score ( $p=0.03$ ).

For the past 3 years, we have also been conducting a randomized controlled trial at Fudan Cancer Hospital examining the effects of acupuncture on prevention of radiation-induced xerostomia. Eighty-five patients were randomized to receive either acupuncture three times a week during radiotherapy or standard care. All patients were treated following the same treatment plan, as proposed in the current study. Self-report assessments were collected weekly for the 7 weeks of radiotherapy and on week 11 (1 month after radiotherapy) and 6 months post treatment. Saliva flow using unstimulated and stimulated whole saliva flow rates

was measured at baseline and weeks 1, 3, 4, 6, 7, and 11 and 6 months post acupuncture/radiotherapy. On weeks 3 and 6 the saliva tests were conducted before the acupuncture treatments.

As can be seen in Figure 1, starting in week 3 of treatment and lasting through the 1-month follow-up (week 11), the XQ scores were significantly lower for patients who received acupuncture (GLMM analyses, including a quadratic term for time). By the end of treatment and 1 month later, the group differences were 10 points or greater [week 7: acupuncture = 44.2 vs control = 54.5 (effect size = 0.80); week 11 acupuncture = 32.2 vs control = 41.5 (effect size = 0.68)]. Importantly, the mean score in the acupuncture group dropped to just above 30,

which is viewed as a clinically significant response (22, 74). Examination of XQ scores of 30 or above by group using chi square analyses showed that by week 11, the acupuncture group had significantly fewer patients with scores over 30 suggesting clinically significant differences (week 11- acupuncture 60.0%; control 88.4%,  $P < 0.004$ ). In addition, the effect size differences also suggest clinically significant differences (25, 86, 87). Similar findings are seen in Figures 2 and 3 for quality of life assessed with the MDASI-HN.

[figure not shown]

Figure 1.

[figure not shown]

Figure 2.

[figure not shown]

Figure 3.

Importantly, the measures of saliva flow, both stimulated and unstimulated, also indicated improvement for the acupuncture group (Figure 4). This was true even when the saliva sampling was done before the start of acupuncture treatment, as on

[figure not shown]

Figure 4.

weeks 3 and 6 (sampling done after acupuncture treatment on weeks 1, 2, 4, 5, and 7). Group differences emerged as early as week 2 and remained significant through week 11.

### C.10 Progress Report Since Last Review

The original application was submitted in June 2009. Since then, we have completed a 6-month follow-up of 70 of the original 85 patients from the randomized trial to examine the duration of the response. Although both groups had a reduction in xerostomia symptoms, the difference in XQ scores between groups remained about the same, with lower scores in the acupuncture group (acupuncture = 21.9 vs control = 34.0,  $p < 0.0006$ ). Examination of XQ scores of 30 or above using chi square analyses showed that by 6 months, the acupuncture group had significantly fewer patients with scores over 30 (acupuncture 27.6%; control 63.6%,  $p = 0.005$ ). The group differences in MDASI-HN scores also remained different (MDASI-HN Symptoms: acupuncture = 2.6 vs control = 4.6,  $p = 0.07$ ; MDASI-HN Interference: acupuncture = 2.6 vs control = 4.0,  $p = 0.02$ ). Importantly, 6 months after the end of radiotherapy, the measure of stimulated saliva flow indicated continued improvement for the acupuncture group (acupuncture = 1.57 vs control = 0.95,  $p = 0.003$ ). For unstimulated saliva flow, group means were in the expected direction but were not statistically significantly different (acupuncture = 0.50 vs control = 0.46,  $p = 0.60$ ). The proposed trial will allow us to follow a larger sample size out to 12 months to determine the stability of the response.

Since this grant application was last reviewed, we also completed a small placebo/sham acupuncture trial at Fudan Cancer Hospital in order to demonstrate the feasibility and examine initial efficacy. This pilot trial used a design similar to that of the previous trial and the one outlined in the proposed study, including the inclusion/exclusion criteria (e.g., patients undergoing IMRT). Of the 30 eligible patients approached, 21 patients consented and were randomly assigned to real or sham acupuncture. The recruitment rate was similar to that in the previous study, and the research nurse remained blinded to group assignment. The XQ was collected weekly starting at baseline for the duration of radiotherapy and then again 1 month later. Salivary flow rate was collected at baseline, and weeks 1, 3, 4, 6, and then again 1 month later. Although the main purpose of this pilot trial was simply to show feasibility of doing a placebo-controlled trial, initial examination of the data suggests improved outcomes for the true versus sham acupuncture. In fact, the findings were remarkably similar to the previous trial, with the expected lower rate of xerostomia symptoms for both groups due to patients undergoing IMRT. However, there were significant group differences starting in week 3 for XQ levels (see Figure 5). The saliva flow outcomes were in the expected direction, but due to the small sample size and high variance, differences did not reach statistical significance (see Figures 6 and 7).

[figure not shown]

Figure 5.

[figure not shown][figure not shown]

2033  
2034 The sham group remained blinded, with all patients believing they were in the active  
2035 acupuncture group. Importantly, there was no indication that the sham treatment protocol had  
2036 an impact on the development of xerostomia (similar outcomes to the standard care group  
2037 from the previous trial, although slightly diminished XQ score due to IMRT). However, a larger  
2038 trial is necessary to confirm that the placebo treatment group is in fact similar to the standard  
2039 care group. Based on the positive findings on subjective (XQ) and objective (salivary flow)  
2040 measures from the previous trial that compared acupuncture to standard care, it is important  
2041 at this stage to conduct a large phase III clinical trial, as outlined in the proposed study,  
2042 comparing true acupuncture to sham acupuncture and standard care.

2043  
